#### ***Hypotheses***

With the primary aim of testing the effect of messages about VLNCs accompanied with VLNC use (vs. use of VLNCs without messages) on the number of cigarettes smoked per day, we hypothesize that participants exposed to messages in combination with VLNC use will smoke fewer study and non-study cigarettes per day compared to those using VLNCs without receiving any messages.

The second aim is to examine the effect of messages about VLNCs in combination with VLNC use (vs. use of VLNCs without messages) on the use of other tobacco products (e.g., cigarillos, e-cigarettes), cigarette dependence, and cessation-related outcomes over the study period. We hypothesize that exposure to messages in combination with VLNC use will lead to (1) less non-study cigarette use, (2) less cigarette dependence, and (3) an increase in the forgoing of cigarette behaviors compared to VLNCs without messages. The third aim is to examine the effect of messages about VLNCs in combination with VLNC use (vs. use of VLNCs without messages) on perceptions and behavioral intentions. We hypothesize that exposure to messages in combination with VLNC use will lead to (1) increased perceived risk of smoking VLNCs, (2) increased self-efficacy to quit smoking, and (3) increased intention to quit or cut down smoking compared to VLNCs without messages.

### Harms {17}

An adverse event (AE) is defined as any unfavorable and unintended diagnosis, symptom, sign, syndrome, or disease which either occurs during the study, having been absent at baseline, or if present at baseline, appears to worsen. Adverse events are to be recorded regardless of their relationship to the study intervention. A serious adverse event (SAE) is defined as any untoward medical occurrence that results in death, is life threatening, requires inpatient hospitalization or prolongation of existing hospitalization, results in persistent or significant disability/incapacity, or is a congenital anomaly. The study coordinator at each site will conduct daily oversight of participant safety and will meet regularly with the PI to review progress and discuss any problems or concerns. Adverse events that are not deemed “serious adverse events” will be included in the final report to the investigators, Institutional Review Board (IRB), and National Cancer Institute (NCI).

SAEs that are unanticipated, serious, and possibly related to the study intervention will be reported to the IRB and NCI in accordance with requirements. Georgia State University defines an unanticipated event as an event that was (1) unforeseen; (2) more likely than not related to the research; and (3) either caused harm to participants or others or placed them at increased risk of harm. Unanticipated events include any harm or injury (physical, psychological, social, or economic) or other unexpected events occurring during the course of participation in a research study. As required by the GSU IRB, the PI will report a summary of each unanticipated event to the IRB using the IRB Unanticipated Event form within 7 business days.

Unexpected fatal or life-threatening SAEs related to the intervention will also be reported to the NCI Program Officer and investigators within 7 days. Other serious and unexpected AEs related to the intervention will be reported to the NCI Program Official within 15 days. Anticipated or unrelated SAEs will be handled in a less urgent manner but will be reported to the IRB and NCI.

### Participant timeline {18}

A participant’s direct study involvement is 6 weeks, including 1 week of screening, 1 week of baseline, and 4 weeks of the trial (randomization and weekly visits). There may be some variation due to scheduling constraints. The duration of the study recruitment period will be approximately 48 months. The duration to complete all study procedures and initial data analysis is estimated to be 60 months (48 months to complete the intervention and weekly visits; an additional 6 months for primary data analysis and an additional 6 months for other analysis). Study assessments and schedule are outlined in Table 2.

**Table 2 Tab2:** Schedule of assessments

Variable/timepoint	Baseline visit	Randomization visit	Weekly visit 1–3	Weekly visit 4	Daily log (online)
**Outcomes**					
Cigarettes per day	x				x
Use of other tobacco products	x				x
Use of cessation medications	x				x
Forgoing cigarettes					x
Quit attempts	x	x	x	x	
Perceived risk of VLNCs	x	x	x	x	
Self-efficacy	x	x	x	x	
Quit intention	x	x	x	x	
Nicotine dependence	x	x	x	x	
Cigarette evaluation	x	x	x	x	
Carbon monoxide	x	x	x	x	
**Individual characteristics**					
Demographics	x				
Smoking status	x				
Past quitting	x				
Other tobacco products use	x				
SPD	x	x	x	x	
Pre-existing readiness to quit	x				
**Health monitoring**					
Alcohol and drug use	x	x	x	x	
Health changes		x	x	x	
Respiratory health	x	x	x	x	

### Sample size {19}

In the randomized clinical trial, participants will be randomized into one of two conditions: treatment (VLNCs with messages) or control (VLNCs only). We will conduct three separate trials, each targeting a specific group of people who smoke: (1) individuals with serious psychological distress (SPD), (2) individuals with low SES (defined as having a high school education or less or with household income less than 200% of the federal poverty level), and (3) individuals who are neither of those two groups. For each group, we will have 262 participants to complete the 4-week study. This number accounts for a 20% attrition during the 1-week baseline and an additional 20% attrition during the study period; thus, we will enroll 410 participants and randomize 328 participants to achieve 262 completes for each smoker group. The projected attrition rates are conservative and are based on our own studies and past RCTs with VLNCs [39–41], including with the same priority populations (e.g., 24% attrition during an intensive 8-week study that used ecological momentary assessments in the similar populations in Atlanta, GA [42]; 18% attrition for a 12-week study with smokers with low SES and mental health conditions [13]).

Based on the above assumptions and adjusting for missing data (0–20%) in daily logs, with 262 participants in each participant group completing our study, we will be able to detect the following effect sizes. For data collected in daily logs (28 observations per person): primary outcome (cigarettes per day) and secondary outcomes (use of other tobacco products, cessation medications, and foregoing cigarettes), the study has sufficient (0.80) power to detect small effect sizes (*d* = 0.11–0.17, depending on the level of autocorrelations and missing data). For data collected in weekly in-person visits (5 observations per person): secondary outcomes related to cessation behaviors, perceptions, and physiological responses, the study has sufficient power to detect small-to-medium effect sizes (*d* = 0.27–0.38, depending on the level of autocorrelations and missing data). Cohen’s definition of effect sizes will be used (small *d* = 0.20, medium *d* = 0.50, large *d* = 0.80 [43, 44]).

For binary outcomes, such as making a quit attempt, we will be able to detect odds ratios (OR) between 1.27 and 1.41 for daily log data (28 observations per person, depending on the level of autocorrelations and missing data) and OR = 1.74–2.22 for weekly data (5 observations per person). Past research found baseline values of 35% for the proportion of participants who tried to quit using VLNCs [41]. We will be able to detect small effect sizes (small OR = 1.68, medium OR = 3.47, large OR = 6.71 [45]).

Overall, the study is sufficiently powered to detect small effect sizes, which is necessary based on past research that found that messaging campaigns have at most small effects [46, 47].

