**Methods:**

This multi-site, open-label, parallel-arm RCT will enroll 1230 adults who smoke (*n* = 410 per group: with SPD, low SES, neither category). After a 1-week baseline period, participants will be randomized (1:1) to receive either (1) VLNCs with messaging or (2) VLNCs only (control). Messaging will include pack inserts and digital ads shown during weekly visits to address misperceptions and encourage quitting. Participants will complete daily logs via text messages and attend weekly visits over 4 weeks for data collection, including self-reported smoking behavior, expired carbon monoxide (CO) samples, and questionnaire assessments. The primary outcome is the number of cigarettes smoked per day in the final study week (week 4). Secondary outcomes include the use of other tobacco products, nicotine dependence, forgoing cigarettes, and quit intentions.

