### Outcomes {16}

#### Primary outcome

The primary outcome is the average number of cigarettes smoked per day (study and non-study cigarettes) based on 7 days’ daily logs submitted through text message prompted surveys during the last week of the trial (before the week 4 visit).

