## Statistical methods

### Statistical methods for primary and secondary outcomes {27a}

We will conduct intent-to-treat analysis. All participants who were originally assigned to different treatment conditions are analyzed as part of their original conditions, regardless of whether they completed the treatment or adhered to the protocol. Analyses will be performed using SAS or R software. All statistical tests will be two-tailed (*α* = 0.05). The treatment condition will be compared to the control condition; if significant differences are observed (*p* < 0.05), the results will be interpreted as evidence of treatment effect.

Descriptive statistics for all measurements will be reported separately for each trial (people who smoke with SPD, with low SES, and with neither). Frequency distributions will summarize categorical data, and measures of central tendency and dispersion will summarize continuous data. All data will be examined for bivariate relationships with the outcomes and with each other.

For each trial, the primary analysis will be regression models to test the difference in the mean CPD (cigarettes smoked per day) between those in the treatment condition and those in the control condition, adjusting for the baseline CPD value and other covariates that are strongly correlated with the outcome (*r* ≥ 0.3) [49]. Analyses of secondary outcomes will be similar to the analysis of the primary outcome. We will use multivariable regression models to examine differences between the treatment and the control arm while accounting for potential covariables.

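### The stated primary-outcome power (d = 0.11–0.17) assumes 28 daily observations per person, but the primary outcome is the mean of the 7 week-4 logs, so the range is not the power of the planned analysis

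*Protocol article*

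**What the plan says.** The protocol article's Sample size section {19} sets 262 completers in each of three separate trials. It groups the daily-log outcomes as "For data collected in daily logs (28 observations per person): primary outcome (cigarettes per day) and secondary outcomes", and for that group says that "the study has sufficient (0.80) power to detect small effect sizes", with d given as "0.11–0.17, depending on the level of autocorrelations and missing data". The autocorrelation values are not stated, and neither is the SD in which d is measured. The section closes by concluding that the study has enough power for small effects, and says this is needed because messaging campaigns have small effects at best. It uses Cohen's small d = 0.20.

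The Primary outcome section reads: "The primary outcome is the average number of cigarettes smoked per day (study and non-study cigarettes) based on 7 days’ daily logs", taken in the last week before the week 4 visit. The abstract agrees: "The primary outcome is the number of cigarettes smoked per day in the final study week (week 4"). Section {27a} states, for each trial, that "the primary analysis will be regression models to test the difference in the mean CPD (cigarettes smoked per day") between arms, adjusting for baseline consumption and for other covariates correlated at 0.3 or more with the outcome. It also says "All statistical tests will be two-tailed", at 0.05.

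Under Secondary outcomes, use of other tobacco products and of cessation medication is likewise based on the last 7 daily logs. Forgoing cigarettes is based on logs from all 4 weeks.

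**The concern.** The power statement credits the primary outcome with four times as many daily values as its definition uses. The article describes no analysis of the primary outcome over all 28 days, so as written the logs of weeks 1–3 do not enter it. Averaging 28 correlated days gives a smaller variance than averaging 7, so a range that depends on 28 days looks more favourable than the planned comparison can deliver. Other tobacco products and cessation medication share the mismatch; forgoing cigarettes does not.

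At stake is the claim that each trial can detect small effects. The results are meant to inform regulators, and section {28b} foresees re-estimating the sample size. Both a null result and a re-estimation would be judged against a detectable effect that belongs to a different analysis.

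**Working it through.** **Inputs.** From {19}: 262 completers per group, power 0.80, 28 observations, d = 0.11–0.17. From Trial design {12}: 1:1 allocation, so 131 per arm. From {27a}: two-sided 0.05. From the Primary outcome section: 7 logs.

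**Attrition chain.** 262/0.8 = 328 and 328/0.8 = 410. This reproduces.

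**Formula.** Detectable effect = (1.960 + 0.842) × √(2V/n), where V is the variance of the value analysed per person, in the chosen SD units squared. With n = 131 and V = 1: 2.802 × √(2/131) = 0.346 (0.347 with the t distribution).

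**The plan's own range.** It cannot be reproduced directly because the autocorrelations are not given, but it can be solved backwards. For d = 0.11, V = (0.11/0.346)² = 0.101; for d = 0.17, V = 0.241.
- Exchangeable correlation, V = (1 + 27ρ)/28: ρ = 0.07 and 0.21.
- AR(1) over 28 days: ρ = 0.50 and 0.77.

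So the range is attainable in single-day SD units when 28 values per person are used.

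**Scale 1: SDs of the 7-day mean.** One value per person, V = 1. Unadjusted, the detectable d is 0.346. With baseline adjustment it is 0.346 × √(1 − r²), where r is assumed because the article gives none.

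| Assumed r | Detectable d | Power at 0.11 | Power at 0.17 | Power at 0.20 |
|---|---|---|---|---|
| 0 (unadjusted) | 0.35 | 14% | 28% | 37% |
| 0.5 | 0.30 | 18% | 36% | 46% |
| 0.7 | 0.25 | 24% | 49% | 62% |
| 0.8 | 0.21 | 32% | 63% | 77% |

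On this scale, 80% power at 0.17 needs r = √(1 − (0.17/0.346)²) = 0.87, and at 0.11 it needs r = 0.95. If all 164 randomised per arm supplied full information, the unadjusted figure would fall only to 0.309.

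**Scale 2: single-day SDs, unadjusted, 7 days instead of 28, at the back-solved correlations.**
- Exchangeable, V = (1 + 6ρ)/7 = 0.201 and 0.325: detectable d = 0.155 and 0.197. Power at 0.11 and 0.17 is 51% and 67%.
- AR(1), V = 0.345 and 0.605: detectable d = 0.203 and 0.269. Power is 33% and 42%.

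**Scale 2, adjusted for a 7-day baseline mean, exchangeable correlation.** The baseline-to-week-4 covariance is ρ, so the residual variance is V − ρ²/V.
- ρ = 0.068: 0.2009 − 0.0228 = 0.178, detectable d = 0.146.
- ρ = 0.213: 0.3255 − 0.1395 = 0.186, detectable d = 0.149.

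The maximum over all ρ is 0.150, near ρ = 0.16. Power is about 90% at 0.17 and about 55% at 0.11. Under AR(1) the two weeks lie three weeks apart and are almost uncorrelated, so adjustment gains nothing and 0.20–0.27 stands.

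**The case against.** The strongest objection concerns the scale. The article does not say in which SD d is measured. Comparing 0.35, in SDs of a 7-day mean, with 0.11–0.17, which back-solves in single-day SDs, mixes units. A reader might infer from that comparison that the true detectable effect is two to three times the stated one. The documents do not support this as a general statement: like for like, the unadjusted ratio is about 1.2 to 1.8 (0.197/0.17 to 0.203/0.11). Baseline adjustment is prespecified and baseline-week logs are collected, so under exchangeable correlation the upper end of the range is met. This objection stands, and it limits the size of the finding.

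A second tempting inference is that the implied daily correlations are implausibly low beside those implied by the weekly range of 0.27–0.38. That fails too. The article speaks of autocorrelations, AR(1) values of 0.50–0.77 are not low, and the weekly range covers different outcomes.

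A third objection is that the model's form may be left to an unseen analysis plan. That does not remove the point. The article itself states a power figure for the primary outcome, and its own outcome definition contradicts the number of observations behind that figure. Nor does the sample-size section state that 410 was derived from this range: it derives 410 from 262 by attrition and then reports what 262 can detect. The finding is therefore a wrong stated power, not a wrong enrolment target.

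**Conclusion.** The point holds as a contradiction within the article: 28 observations in the power statement, 7 in the outcome definition and its analysis. The range 0.11–0.17 is not the power of the planned primary comparison.

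The size of the shortfall depends on the scale of d and on correlations that the article does not give. In every case computed, with r up to 0.8 or with the plan's back-solved correlations, the lower end is missed. The upper end is met only with baseline-week adjustment under exchangeable correlation. Very high baseline correlations (0.87 and 0.95 on the scale of the 7-day mean) would rescue the two ends, but the power statement assumes no such thing.

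The conclusion on small effects is likewise conditional. At d = 0.20 it holds in single-day SDs under exchangeable correlation (0.155–0.197). It fails under AR(1), and it fails in SDs of the 7-day mean for r below about 0.82.

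**What to change.** In {19}, restate the detectable effect for the primary outcome as the week-4 7-day mean. Give the SD scale of d, the assumed within-person correlation structure and values, the assumed baseline correlation, and the equivalent in cigarettes per day. Do the same for other tobacco products and cessation medication. Keep a 28-observation figure only for outcomes analysed over all 28 days, such as forgoing cigarettes. Revise the closing conclusion about small effects to match.

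Optionally, prespecify a supportive mixed model over weeks 1–4 with the week-4 contrast, so that the earlier logs contribute.

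The cost is a rewrite of one section and a less favourable stated figure. Enrolment need not change.

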### Randomization, intervention and weekly visits

During the randomization visit (1 week after baseline), participants will be randomized into treatment (VLNCs + messages) or control (VLNCs only). Participants will be randomized using a 1:1 ratio into treatment (VLNCs + messages) or control (VLNCs only). We will use simple randomization with stratification by site, readiness to quit (planning to quit in the next 6 months vs. not), and menthol preference (menthol vs. non-menthol) with no required sample size for any of these strata. During the randomization and weekly visits, participants will complete questionnaires and provide an expired CO sample. At each visit, they will receive a 14-day supply of VLNCs (with or without the inserts, according to the assigned condition). This will ensure adequate availability of cigarettes in the different locations where participants may typically keep a supply (home, work, vehicle, etc.) as well as avoid expending the entire supply if they miss a scheduled visit. They will be instructed to return all unused cigarettes and empty cigarette packs each week; empty packs will be saved, and unused packs will be redistributed to the participants during subsequent visits. At each visit, they will see 4 messages about VLNCs (in the treatment condition) or, in the control condition, no messages. At each visit, participants will be counseled about daily log completion (based on staff review of compliance during the prior week), visit attendance, and returning unused cigarettes. Throughout the 4 weeks of the study, participants will continue to complete daily logs. During the last visit (end of week 4), participants will be referred to smokefree.gov and given a Quitline number.

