### Secondary outcomes

The following outcomes will be based on 7 days’ daily logs submitted through text message prompted surveys during the last week of the trial (before the week 4 visit). Use of other combusted (e.g., little cigar and cigarillos) and noncombusted (e.g., e-cigarettes) products will be assessed by asking participants to enter an integer indicating the number of each product used per day. Use of nicotine replacement therapy (NRT) or prescription cessation medications will be assessed using a multiple-choice question, allowing participants to select all NRT or prescription cessation medications used from a provided list of options.

The following outcomes will be based on a questionnaire completed during the week 4 visit. Perceived risks of smoking VLNCs will be measured by asking participants’ perceived likelihood of overall harm to health under conditions of smoking VLNCs [33]. Response options range from 1 (Not at all likely) to 5 (Extremely likely), with higher scores representing a better outcome. An additional option, “Don’t know,” is also provided. Self-efficacy to quit smoking will be measured with multiple items, assessing perceptions about the strength of confidence in one’s ability to quit smoking [34]. Response options range from 1 (not at all) to 7 (extremely), with higher scores representing a better outcome. An additional option, “Don’t know,” is also provided. Nicotine dependence will be assessed using the Fagerstrom Test for Nicotine Dependence scale, a six-item questionnaire measuring the quantity of cigarette consumption, the compulsion to use, and dependence [35].

Forgoing cigarettes will be assessed using daily logs submitted throughout the 4 weeks of the trial, with two items asking whether participants chose to skip cigarettes they normally would have smoked and whether they stubbed/butted out a cigarete before finishing it [34, 36]. Response options are as follows: 1 (no), 2 (yes, once), and 3 (yes, several times), with higher scores representing a better outcome. Quit intention will be measured with multiple items asking participants’ intention and motivation to quit in the next month and 6 months [37]. Response options range from 1 (not at all) to 7 (extremely), with higher scores indicating a strong intention to quit. An additional option, “Don’t know,” is also provided.

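### The detectable effects for 28 daily logs and for 5 weekly visits imply one common variance inflation and cannot both be right

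*Protocol article*

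**What the plan says.** The protocol article, Sample size {19}, plans each of the three trials on the same number: "For each group, we will have 262 participants to complete the 4-week study". For daily-log outcomes, counted as 28 observations per person, it states that "the study has sufficient (0.80) power to detect small effect sizes", with d = 0.11-0.17. For weekly-visit outcomes, counted as 5 observations, it states that "the study has sufficient power to detect small-to-medium effect sizes", with d = 0.27-0.38. For binary outcomes it gives "odds ratios (OR) between 1.27 and 1.41 for daily log data" and 1.74-2.22 for weekly data, and quotes a 35% proportion from earlier research.

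Both ranges are said to depend on autocorrelation and missing data, and 0 to 20% of daily logs are allowed to be missing. No correlation value or structure is given. The section ends by concluding that the study is adequately powered for small effects, and calls this necessary because messaging campaigns have at most small effects.

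Secondary outcomes says: "Forgoing cigarettes will be assessed using daily logs submitted throughout the 4 weeks of the trial". So at least one outcome does use all 28 logs. The analysis section plans regression "adjusting for the baseline CPD value and other covariates that are strongly correlated with the outcome", with secondary outcomes analysed similarly.

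**The concern.** Repeated measurements on one person help only to the extent that they are not copies of each other. If people differ persistently, the inflation relative to independent observations grows with the number of observations, so 28 logs should carry a much larger inflation than 5 visits. If correlation instead fades with time, logs a day apart should be more alike than visits a week apart. The stated figures follow neither pattern: the two ranges differ by roughly sqrt(28/5) and by little else.

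The daily-log range carries the conclusion about small effects. The weekly range lies wholly above the protocol's own benchmark for small, d = 0.20. If the daily range is too favourable, that conclusion loses its support. If the weekly range is wrong, the sensitivity for perceptions, dependence and quit intention is misstated.

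**Working it through.** **Inputs.** 262 completers per trial (Sample size {19}); 1:1 allocation (Randomization, intervention and weekly visits), so 131 per arm; 80% power (Sample size {19}); alpha 0.05, "All statistical tests will be two-tailed" (Statistical methods {27a}); m = 28 or 5. I take d to be in units of the standard deviation of a single observation.

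**One observation per person.** d1 = (1.960 + 0.842) × sqrt(2/131) = 2.8016 × 0.1236 = 0.346. On the log-odds scale at 35%: 2.8016 × sqrt(2/(131 × 0.35 × 0.65)) = 0.726.

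**Implied inflation.** With d = d1 × sqrt(V/m), V = m × (d/d1)². For odds ratios, V = m × (ln OR/0.726)².

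| Stated figure | m | V |
|---|---|---|
| d = 0.11 | 28 | 2.83 |
| d = 0.17 | 28 | 6.75 (5.40 if 20% of logs are missing) |
| d = 0.27 | 5 | 3.04 |
| d = 0.38 | 5 | 6.03 |
| OR 1.27 | 28 | 3.04 |
| OR 1.41 | 28 | 6.28 |
| OR 1.74 | 5 | 2.91 |
| OR 2.22 | 5 | 6.04 |

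The weekly-to-daily ratios are 2.45 and 2.24 for d, and 2.32 and 2.32 for ln OR, against sqrt(28/5) = 2.37.

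**Reproducing the plan's figures.** A common V = 3 gives d = 0.113 (m = 28) and 0.268 (m = 5). A common V = 6 gives 0.160 (0.169 with 10% of logs missing, 0.179 with 20%) and 0.379. The stated ranges are therefore recovered from one inflation of about 3 to 6, which is an inference because the article states none.

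**Check 1: the weekly upper end.** For any correlation, the mean of five complete, equally variable observations cannot vary more than one of them, so V cannot exceed 5. The figure 0.38 needs V = 6.03 and exceeds the single-visit value of 0.346.

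**Check 2: correlation at one week's spacing.**
- Exchangeable, V = 1 + (m-1)ρ. Daily: ρ = 1.83/27 = 0.07 to 5.75/27 = 0.21. Weekly: ρ = 2.04/4 = 0.51 at d = 0.27, and 5.03/4 = 1.26 (impossible) at d = 0.38.
- AR(1), V = 1 + 2 Σ(1 - k/m)r^k. Daily: day-to-day r = 0.50 at d = 0.11 and 0.77 at d = 0.17 with no missing logs (0.72 with 20% missing). Seven days apart this is 0.01 to 0.17 (0.10 with 20% missing). Weekly: r = 0.69 from one visit to the next at d = 0.27, with no solution at 0.38.

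**Check 3: carrying the lowest visit-implied correlation to 28 logs.**
- Exchangeable, ρ = 0.51: 0.346 × sqrt((1 + 27 × 0.51)/28) = 0.25.
- AR(1): daily r = 0.69^(1/7) = 0.949, V = 18.2, d = 0.346 × sqrt(18.2/28) = 0.28.

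**Illustration only** (assumed exchangeable ρ, no baseline adjustment, 28 logs): ρ = 0.3, 0.5, 0.7 gives d = 0.20, 0.25, 0.29. At ρ = 0.5, power is about 24% at d = 0.11 and 48% at d = 0.17.

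**The same illustration with baseline adjustment.** Assume that seven baseline-week logs of the same item share ρ. With v = (1 + 27ρ)/28, b = (1 + 6ρ)/7 and R² = ρ²/(vb), d = 0.346 × sqrt(v(1 - R²)) = 0.109, 0.098, 0.078 for ρ = 0.3, 0.5, 0.7.

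**The case against.** The article speaks of autocorrelation, not of an intraclass correlation. Exact AR(1) over 28 logs with day-to-day r = 0.5-0.7 gives 0.111-0.148, or 0.124-0.165 with 20% of logs missing, close to the stated range. The long-series factor (1+r)/(1-r) at the same r gives 0.268-0.369 for 5 visits, close to the weekly range. On this reading the daily figures are sound and the fault is in the weekly ones: a correlation for one-day steps is reused for one-week steps, and a long-series factor is applied to five points, where the exact calculation gives 0.231-0.272. This stands as a plausible origin. It confirms that the two ranges do not belong together, but it prevents naming the daily range as the wrong one.

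A reader might infer that forgoing cigarettes is in truth powered only for d = 0.20-0.29. The documents do not support that. It needs an assumed exchangeable ρ of 0.3-0.7 and no baseline adjustment. Nor do they establish that forgoing has no baseline value: daily logs run from the baseline period, and Table 2 lists forgoing under the daily log without limiting the phase. With such a covariate the figure could fall to 0.08-0.11, although the switch from normal- to low-nicotine cigarettes may weaken the baseline correlation. Likewise, low autocorrelation might describe residuals after adjustment, so it need not make baseline CPD a poor predictor.

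Two further defences have some force. Missing data might explain 0.38: if 20% of people, not logs, are lost (about 210 left), one visit gives 0.387 and 0.38 needs ρ = 0.955. But 262 is already the number after attrition, and losing visits instead (m = 4) still needs ρ = 1.27. Logs and visits also measure different outcomes, which could differ in persistence. Nothing in the article says they do, and the near-identical inflation suggests one assumption for both.

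An article may leave the correlation model to the full protocol. The detectable effects, however, are printed here, and a conclusion rests on them.

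**Conclusion.** The concern holds as an inconsistency between two stated ranges. Daily and weekly figures, on both the d and the OR scale, rest on essentially one inflation of about 3 to 6. The weekly 0.38 is unattainable with five complete visits in 262 completers. The other figures need a week-apart correlation of at most about 0.2 for logs (0.17 under AR(1), 0.21 if exchangeable) and at least about 0.5-0.7 for visits. If the visit-implied correlation is right, the unadjusted 28-log detectable d is about 0.25-0.28, not 0.11-0.17.

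This rests on back-solved inflations, on d in single-observation units, and on logs and visits being similarly persistent. Only the bound on 0.38 is free of the last assumption. Which range is wrong, and the true detectable effect for forgoing, cannot be settled from the document. The point is also separate from the number of logs an outcome uses. The primary outcome is defined on the last 7 days only, which is a different question.

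**What to change.** In Sample size {19}, state the assumed correlation, its structure, how missing data enter, and any baseline adjustment with the baseline correlation it relies on. Recompute both the daily and the weekly ranges, d and OR, under one coherent model: a person effect plus AR(1) with the lag in days, or 1 + (m-1)ρ. Where the item is collected in the baseline week, estimate the correlation from those logs, pooled and blind to arm. Then restate the conclusion about power for small effects to match the recomputed figures.

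The cost is one recalculation and a few sentences. The stated figures may become less favourable. Enrolment does not change.
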